#### Short Physical Performance Battery

Lower extremity function will be measured with the Short Physical Performance Battery (SPPB). The SPPB is a group of measures including gait speed, chair stand, and balance tests. For each test, a 5-level categorical score will be assessed, with 0 representing inability to complete the test and 4 representing the highest level of performance. The summary score ranges from 0 (worst performance) to 12 (best performance). The SPPB has been shown to have good predictive validity, has been used in the RA population before, and can be used as a predictive tool for possible disability and mortality in older people [46-49].

#### Medical Outcomes Study Sleep Scale

The patients’ quality of sleep will be assessed with the Medical Outcomes Study Sleep Scale (MOS-SS) questionnaire, which was created as a part of the Medical Outcomes Study, a large public health initiative that also developed practical tools for the routine monitoring of patient outcomes [50].

The MOS-SS is a 12-item self-report questionnaire involving a retrospective assessment over the past 4 weeks. The MOS-SS measures 6 sleep dimensions: (1) initiation (time to fall asleep in minutes), (2) quantity (hours of sleep each night), (3) maintenance, (4) respiratory problems, (5) perceived adequacy, and (6) somnolence. The last 4 items will be assessed via a 6-item scale ranging from “all the time” to “none of the time” [51].

The questionnaire yields 2 sleep problem indexes and 6 scores, of which sleep problem indexes I and II and the sleep disturbance scale were shown to have acceptable validity in RA patients [52]. Furthermore, the MOS-SS has been applied in several arthritis studies, and its good reliability and validity have been established [53]. Additional questions will assess the significance of pain in sleeping difficulties and the frequency of pain and sleep medication use.

#### Sexual Functioning

Sexual functioning will be measured via a self-assessment questionnaire individually designed for this study. Standardized questionnaires on sexual functioning such as the questionnaire for screening sexual dysfunctions or gender-focused questionnaires such as the Female Sexual Function Index are extensive and very detailed. For questions related to sexuality, people tend to react apprehensively, so data collection (completion of the questionnaires) will be conducted in the rheumatology outpatient department (not as an online or mail survey). A short screening tool that focuses on the main problems that RA patients face with regard to sexual function was created.

Based on a recent review [25] and a multicenter study [54] on the impact of RA on sexual function, the questionnaire was designed consisting of 2 sections addressing sexual disability (difficulties in performing sexual intercourse), represented by question 1, and sexual drive (reflected in sexual desire and satisfaction), represented by questions 2 to 5. Scoring ranges from 1 to 10, and anchor points are set according to the question. The overall sexual functioning score ranges from 5 points (poor sexual functioning) to a maximum of 50 points.

### Statistical Analysis

All statistical computations will be performed with SPSS version 22.0.2 (IBM Corp). The primary hypothesis of the study, “A difference in work ability and muscle strength exists in patients with high versus low disease activity,” will be tested with a Pearson chi-square test. For the descriptive statistics, mean values will be calculated for continuous variables, and categorical variables will be presented in percentages. Continuous parameters will be checked for normal distribution (Kolmogorov-Smirnov test, Levene test, histogram, and Q-Q plot check), and an unpaired Student *t* test will be performed, as appropriate. Otherwise, the Mann-Whitney U test will be used to identify differences between patients with high versus low disease activity. For categorical parameters, a Pearson chi-square test or Fisher exact test will be used if the cell count is <5. Binary logistic regression will be used to evaluate the impact of frailty, functional ability, and muscle strength on work ability. For metric data, Pearson correlation or Spearman rank correlation (given outliers or nonlinear but monotone associations) will be used to evaluate associations of interest. A *P* value of <.05 will be considered statistically significant for all tests.

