### Rheumatoid Arthritis and Sexual Functioning

All aspects of life may be affected by RA. Pain, stiffness, and fatigue may impair not only functional disability but also sexual functioning in RA patients. As summarized by a recent review, aside from functional problems, depression, anxiety, a negative body image, reduced libido, and the application of certain drugs can negatively influence sexual activities [25].

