### Aims and Objectives

The primary objective is to assess work ability in patients with seropositive RA in the working age and the association of work ability with disease activity (high, medium, low, or remission). The secondary objectives are to assess the association of muscle strength, lower extremity function, functional ability, and frailty with work ability in RA and determine the association of disease activity with selected physiological needs (sleep quality, sexual functioning) in RA.

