### Data Collection and Procedures

Demographic, clinical data, and disease activity will be assessed through clinical examination and administration of an interview questionnaire. The demographic characteristics include gender, age, marital status (married/common law, single/widowed/ divorced), highest level of education (compulsory schooling, secondary school graduation, higher education), and type of occupation.

Disease-specific clinical characteristics include disease duration (months) and current medication use for each of the following categories: analgesics/nonsteroidal anti-inflammatory drugs, disease-modifying antirheumatic drugs, biologic agents (biologicals), and drugs for other medical conditions.

Pain will be assessed via a visual analog scale (VAS), a unidimensional measure of pain intensity that has been widely used in diverse adult populations, including those with rheumatic diseases. The VAS consists of a 10 cm line anchored by verbal descriptors (1=no pain at all, 10=maximum pain) [34]. The patient will be asked to place a line perpendicular to the VAS line to indicate his or her current pain intensity.

Overall disease activity will be measured with the Clinical Disease Activity Index (CDAI). The CDAI is validated and widely used [35], with the scoring done as per the following formula: CDAI = SJC-28 + TJC-28 + PGA + EGA, where SJC-28 is the Swollen 28-Joint Count (shoulders, elbows, wrists, metacarpophalangeal joints, proximal interphalangeal joints including thumb interphalangeal joint, knees), TJC-28 is the Tender 28-Joint Count, PGA is the Patient Global Assessment (patient’s self-assessment of the overall RA disease activity on a scale of 1 to 10, where 10 is the maximal activity), and EGA is the Evaluator’s Global Assessment (evaluator’s assessment of the overall RA disease activity). As proposed by the American College of Rheumatology 2008, the CDAI score will be interpreted as follows: remission = CDAI ≤ 2.8, low disease activity = CDAI > 2.8 and ≤ 10, moderate disease activity = CDAI > 10 and ≤ 22, and high disease activity = CDAI > 22.

Laboratory assessments include CRP (mg/dL), IL-6 (pg/mL), and TNF-α (ng/mL). For the detection of IL-6 and TNF-α, high-sensitivity enzyme-linked immunosorbent assay will be used, assayed in duplicates. The CRP will be measured with the patients’ routine laboratory assessments. Blood samples will be analyzed at the Institute for Laboratory Medicine of the SMZ-Süd, Vienna, Austria.

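### Disease activity is related to sexual functioning and sleep only by unadjusted tests or correlations, so any part played by age, sex or recorded drug use would not be seen

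*Protocol article*

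**What the plan says.** The Aims and Objectives section of the protocol article makes it a secondary aim to "determine the association of disease activity with selected physiological needs (sleep quality, sexual functioning) in RA".

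The Statistical Analysis section names these methods that could serve that aim:

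- For continuous parameters, an unpaired t test where its conditions hold. "Otherwise, the Mann-Whitney U test will be used to identify differences between patients with high versus low disease activity".
- For grouped outcomes, a contingency-table test without covariates (Pearson chi-square, or Fisher exact where cells are small).
- For metric data, Pearson correlation or "Spearman rank correlation (given outliers or nonlinear but monotone associations) will be used to evaluate associations of interest".

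One regression is named, for a different outcome: "Binary logistic regression will be used to evaluate the impact of frailty, functional ability, and muscle strength on work ability".

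Three other places bear on the choice:

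- The Introduction, on sexual functioning, lists several influences and includes that "the application of certain drugs can negatively influence sexual activities".
- Data Collection and Procedures records age and gender, and current use of "analgesics/nonsteroidal anti-inflammatory drugs, disease-modifying antirheumatic drugs, biologic agents (biologicals), and drugs for other medical conditions".
- The section on the sleep scale adds: "Additional questions will assess the significance of pain in sleeping difficulties and the frequency of pain and sleep medication use".

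No stated analysis uses age, gender or any of the drug data.

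**The concern.** High and low disease activity are observed states, not assigned ones. Patients in the two groups may differ in age, sex and treatment, and each of these may bear on sexual functioning or sleep. For sexual functioning the protocol itself names drugs as one such influence and collects drug classes. It then specifies tests into which no covariate can enter.

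If the plan is followed as written, a lower sexual functioning score in the high-activity group would be reported as an association with disease activity. The reader would have no means of judging how much of it goes with age, sex or drug exposure. The Discussion hopes that these findings may encourage research and interventions on problems associated with RA, and the likely source of a difference matters for that use.

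**Working it through.** **1. What the plan can and cannot do.** The t test, Mann-Whitney, chi-square and Fisher tests and the bivariate correlations all relate one outcome to one other variable. The single regression has work ability as outcome, and its predictors are frailty, functional ability and muscle strength. Sexual functioning, sleep and drugs are not in it. So no named method gives an adjusted estimate for this objective.

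**2. Inputs for size.** The plan states no figure for this objective, so there is none to reproduce. From the Sample Size section I take 70% of participants with low activity and 100 patients included, and treat the rest as high: n_H = 30, n_L = 70. Everything else is an assumption:

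- p_H and p_L: share of each group using a drug class that affects the score.
- d: reduction in the score caused by that drug, in SD units.
- No true disease-activity effect, and a residual SD of 1.

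**3. Formulas.**

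- Expected group difference: B = d × (p_H − p_L).
- Standard error: SE = √[(1 + d²p_H(1 − p_H))/n_H + (1 + d²p_L(1 − p_L))/n_L].
- Two-sided rejection rate: 1 − Φ(1.96 − B/SE) + Φ(−1.96 − B/SE).

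**4. One case in full** (d = 0.5, 60% versus 20%).

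- B = 0.5 × 0.40 = 0.20 SD.
- SE = √(1.06/30 + 1.04/70) = √(0.0353 + 0.0149) = 0.224.
- B/SE = 0.893, and the rejection rate is 0.145.

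**5. Results.** The simulated columns use 8,000 replicates, comparing a pooled t test with a linear model that contains the drug indicator.

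| Drug use, high / low | d (SD) | B (SD) | Normal approx. | Simulated, unadjusted | Simulated, exact drug term |
|---|---|---|---|---|---|
| 50% / 30% | 0.5 | 0.10 | 0.073 | 0.079 | 0.056 |
| 60% / 20% | 0.5 | 0.20 | 0.145 | 0.142 | 0.048 |
| 60% / 20% | 0.8 | 0.32 | 0.280 | 0.272 | 0.050 |

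A separate simulation with the Mann-Whitney test (4,000 replicates, 60% versus 30% use, N = 100) gave 10% for d = 0.5 and 17% for d = 0.8. At N = 71 the figures were 8% and 14%. With 30% use in both groups, the rate was 4% to 5%.

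**6. How far adjustment helps.** The last column of the table is a best case, because the model contains exactly the drug that acts. The protocol records four broad categories and does not say which drugs matter. Suppose the recorded category also contains unrelated drugs used by 40% to 80% of patients (assumed). With 60% versus 20% use of the causal drug, the adjusted model then still rejects in about 10% to 13% of studies for d = 0.5 and 16% to 25% for d = 0.8. My rerun with 8,000 replicates gave 0.096 to 0.134 and 0.164 to 0.248. Coarse adjustment reduces the problem and leaves much of it.

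The formula for B applies equally to sex, or to any other two-level factor that differs between the groups. The documents give no figures for those either.

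**The case against.** The strongest reply is that the planned tests answer the question asked. The objective speaks of association, and the Strengths and Limitations section disclaims causality and calls the approach suited to generating hypotheses. An unadjusted comparison does estimate the crude association. That stands, and it is why the planned test should stay. It does not dispose of the point: the limitations named are the cross-sectional design and pain-related noncompliance, not confounding by recorded factors.

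Second, treatment is partly a response to disease activity. Conditioning on drug use may then remove part of the association of interest, and one visit cannot separate the directions. This also stands. A drug-adjusted model estimates something different and is not a correction of the crude result. The argument does not touch age and sex, which disease activity does not cause.

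Third, the article condenses a fuller plan, which may hold covariate sets, and it does not tie sleep or sexual functioning to a named test. Both outcomes fall under its general wording on continuous parameters and associations of interest. The article does, however, name the tests by type, and none of them takes a covariate.

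A reader might infer three stronger things that the documents do not support:

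- That the two-group test is wrong and must be replaced. It fits the stated objective.
- That adjusting for the recorded drug classes would restore a 5% error rate. That holds only if the category matches the causal drug.
- That sleep medication hides a sleep difference. The protocol records such medication but nowhere says that it masks anything; its statement on drugs concerns sexual activities only.

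**Conclusion.** The point holds as a gap in a secondary analysis. For disease activity against sexual functioning and sleep, the plan names only unadjusted methods in a non-randomised comparison, while age, gender and drug classes lie recorded and unused. The case is best documented for sexual functioning, where the protocol names drugs as an influence. For sleep it rests on age and sex alone.

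The rejection rates of about 8% to 27% are illustrations. They assume a 30/70 split of 100 patients, drug-use imbalances of 20 to 40 points, drug effects of 0.5 to 0.8 SD and no true disease-activity effect. They are false positives only with respect to an effect of disease activity apart from drugs, which the protocol does not claim to estimate. With equal drug use there is no inflation. The primary result on work ability is not affected.

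**What to change.** Keep the planned unadjusted comparison. Beside it, and labelled as added after enrolment was complete, report:

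1. A linear (or rank-based) regression of the sexual functioning score and of the sleep-scale indexes on disease activity, adjusted for age and sex.
2. For sexual functioning only, a second model that also contains the recorded drug-class indicators. Present it as a sensitivity analysis, and say that treatment partly follows disease activity and that the categories are coarse, so it reduces but does not remove drug confounding.

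An analysis of sleep restricted to patients without regular sleep medication is optional.

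All variables for the two models are already collected. The cost is a few degrees of freedom and some added wording in the analysis section; the optional sleep analysis would also rest on a smaller subset.

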## Introduction

### Background

Rheumatoid arthritis (RA) is a chronic, systemic autoimmune disease that is most prevalent in individuals aged 40 years and above. RA affects about 1% of the world population, and the risk of developing RA is markedly higher in women. This disease is the most common form of chronic joint inflammation and causes joint pain, swelling, reduced muscle strength, and, as a consequence, impaired physical function [1]. In our experience, due to physical limitations, RA patients often suffer from impairment in their social life and their work life. Working is an important predictor of physical health–related quality of life in arthritis patients [2], and reduced muscle strength can cause physical limitations and a more frail condition, which in turn might have an impact on work ability. Beside obvious symptoms that directly cause physical limitations, physicians less often pay attention to physiological needs such as sleep and sexual functioning, which are also negatively associated with RA and in turn might unfavorably impact work ability.

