##### Musculus Quadriceps Femoris Maximum Voluntary Contraction Strength

Quadriceps muscle strength will be measured with an isokinetic dynamometer. The patients will sit straight with 90° flexion in the hips and with fixed hip and thigh support and arms crossed. The ankles will be fixed in a flexed position to the dynamometer, and a measuring box (Chatillon, Ametek Inc) is connected to the ankle via a length-adjustable rope. The patient will be instructed to perform 1 maximal voluntary contraction of the quadriceps muscle. Strength will be assessed 3 times for both legs with a 2-minute break between measurements. The mean value of both legs will be used in the statistical analysis.

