##### Maximal Voluntary Isometric Hand Grip Strength

The maximum grip strength will be measured with a portable Jamar hydraulic hand dynamometer (Patterson Medical). The patients will be examined in a standard position, in which they sit upright with their upper arm adducted and the elbow flexed at 90°. The dynamometer will be used according to the instructions in the operating manual. The dynamometer will be placed in a patient’s hand, and after the instruction is given, 3 maximum voluntary grip strength contractions will be performed with each hand. Measurements will be done in an alternating order with a 2-minute break between measurements. The mean value of each hand will be recorded for analysis.

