#### Survey of Health, Ageing, and Retirement in Europe Frailty Instrument

Frailty will be assessed with the Survey of Health, Ageing, and Retirement in Europe Frailty Instrument (SHARE-FI). This instrument was developed on the basis of the results of the Survey of Health, Ageing and Retirement in Europe and serves as a rapid measurement tool with good predictive validity. The assessment comprises 5 variables: grip strength measurement and 4 questions related to weakness, exhaustion, slowness, and activity level. With the use of the 5 variables, DFactor scores will be calculated with the gender-specific SHARE-FI formula. For each participant, the frailty score will be computed, and the participants will then be categorized as nonfrail, prefrail, or frail [45].

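### The natural test for muscle strength by disease activity makes no allowance for sex, and the hypothesis sentence assigns strength a chi-square test without a cut-off

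*Protocol article*

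**What the plan says.** The Statistical Analysis section states as the primary hypothesis: "A difference in work ability and muscle strength exists in patients with high versus low disease activity". It assigns a Pearson chi-square test to that hypothesis. No section gives a cut-off that would turn strength into a categorical variable.

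For continuous parameters in general, the same section checks normality and then says "an unpaired Student *t* test will be performed, as appropriate". If that does not apply: "Otherwise, the Mann-Whitney U test will be used to identify differences between patients with high versus low disease activity". Neither sentence names a covariate or a stratum.

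The strength variables are dynamometer means. For the quadriceps, "The mean value of both legs will be used in the statistical analysis"; for grip, "The mean value of each hand will be recorded for analysis". No scaling by sex, body size or norm values is stated.

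Elsewhere the protocol does take account of sex. Under Data Collection and Procedures, "The demographic characteristics include gender, age, marital status". In the frailty section, where grip is one of five inputs, "DFactor scores will be calculated with the gender-specific SHARE-FI formula". The Background notes that "the risk of developing RA is markedly higher in women". Both sexes are eligible, and the design is cross-sectional with consecutive inclusion.

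**The concern.** When strength is compared between activity groups, strength is the outcome and disease activity the exposure. The logistic regression in the same section has work ability as its outcome, so it does not bear on this comparison.

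Two things can go wrong if men and women are pooled in a two-sample test on unscaled readings:

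- **Precision.** The difference between the sexes stays in the residual variance, so the test has less power than one that removes it.
- **Confounding.** If the share of women differs between the high and low activity groups, part of the sex gap enters the estimated difference. Disease activity is observed, not assigned, so nothing in the design makes the groups alike in sex.

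The Mann-Whitney fallback removes neither problem. Nor would a chi-square on strength dichotomised at one cut-off for both sexes.

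**Working it through.** **The plan's own figure.** No sample size or power is stated for strength. The Sample Size section gives 71 evaluable patients for work ability (40% vs 80%, 70% in the low group, two-sided 0.05, 80% power). The usual two-proportion formula gives 54, or 64 with continuity correction, so 71 is not reproduced. It matters here only for group sizes: 0.30 × 71 ≈ 21 and 0.70 × 71 ≈ 50. With all 100 included patients measured, the split is 30 vs 70. Treating everyone outside the low group as high is an assumption.

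**Assumed inputs (none is in the documents).** For grip: share of women p = 65-85%, sex gap G = 15-20 kg, within-sex SD s = 6-10 kg, true activity effect 5 kg. Central case: p = 75%, G = 18, s = 8.

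**Variance share of sex** = p(1−p)G² / [p(1−p)G² + s²].
- Central: 0.1875 × 324 = 60.75; 60.75 / (60.75 + 64) = 49%. Pooled SD = √124.75 = 11.17 kg.
- Lowest (p = 85%, G = 15, s = 10): 28.69 / 128.69 = 22%.
- Highest (p = 65%, G = 20, s = 6): 91 / 127 = 72%.

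**Power**, with noncentrality = 5 / [SD × √(1/n₁ + 1/n₂)], using the pooled SD for the plain t test and s for the sex-adjusted model:

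| Case | Pooled | Sex-adjusted |
|---|---|---|
| 30 vs 70, central | 5 / (11.17 × 0.218) = 2.05 → 53% | 5 / (8 × 0.218) = 2.86 → 81% |
| 21 vs 50, central | 5 / (11.17 × 0.260) = 1.72 → 40% | 5 / (8 × 0.260) = 2.40 → 66% |
| 30 vs 70, full range | about 37-80% | about 61-97% |

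Simulation agrees within a point: 53% vs 82% at 30 vs 70 (Mann-Whitney 52%), and 39% vs 65% at 21 vs 50.

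**Milder case.** Take a gap of one within-sex SD, 60-80% women, 21 vs 50 patients, and an effect of 0.73 within-sex SD, which has 80% power when adjusted. Pooled power is then 71-74%, a loss of 6-9 points.

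**False positives with no true activity effect:**
- Same expected sex mix in both groups: about 5%. Pooling alone does not inflate the error rate.
- 85% vs 70% women, central values, 30 vs 70: spurious difference 0.15 × 18 = 2.7 kg; about 19% pooled, 5% adjusted.
- 21 vs 50, gap of 1 to 2.5 within-sex SDs, fixed sex counts: 3-5% at 17 of 21 vs 35 of 50 women (81% vs 70%), 9-20% at 86% vs 64%, and 16-48% at 90% vs 60%. The adjusted model stayed at 5-6% where checked (86% vs 64%).

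**The case against.** The case against has several sound parts.

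- **The t test and Mann-Whitney are not explicitly assigned to strength.** The only sentence that joins strength to disease activity names a chi-square. That stands: the two-sample route is the natural reading for a continuous measurement, not a literal instruction. It also means the chi-square sentence itself needs repair.
- **The comparison has modest standing.** Strength is listed under secondary outcomes, the Aims and Objectives do not include strength by disease activity, the sample size concerns work ability only, and the limitations section presents the study as hypothesis-generating. That stands too, although the hypothesis sentence does name strength.
- **Every strength input is assumed.** A reader might infer that sex overwhelms any activity difference. The documents cannot support that: they give no sex gap or SD, and the loss is small if the gap is near one within-sex SD.
- **No imbalance is shown.** A reader might also infer that the result will be biased. Nothing says the sex mix differs by activity level; the Background statement concerns the risk of developing RA. With a modest difference in mix, the error rate may not rise at all.
- **Adjustment does not make the comparison well powered.** At 21 vs 50 the central case reaches only about 65%.

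One reply does not stand: that this is a detail left to a fuller analysis plan. The article names specific two-sample tests, and neither has room for sex.

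**Conclusion.** The point holds in limited form. The hypothesis sentence gives strength a test that does not fit a continuous variable without a cut-off. The tests that do fit ignore sex, although the protocol records it and allows for it in the frailty score. The likely cost is lost precision. It is material if the sex gap is about two within-sex SDs (53% against 82% power in the central case) and slight if it is about one. A false association is a possibility that depends on an actual sex imbalance, not something the documents demonstrate. All sizes rest on the assumed strength values and on a two-group 30:70 split. The work-ability comparison is not affected. The change is worth making because the covariates are already recorded.

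**What to change.** In the Statistical Analysis section:

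1. Limit the Pearson chi-square test to categorised work ability, and state separately how strength is tested.
2. Compare grip and quadriceps strength between activity groups with a linear model that has sex and age as covariates, and report the adjusted mean difference with a 95% CI. If a rank method is preferred, stratify it by sex (van Elteren). Sex is the covariate that the figures above support; age is a reasonable addition, already recorded, whose effect was not calculated.
3. Keep the unadjusted test as descriptive, and tabulate the sex mix by activity group so that readers can see whether confounding arises.

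Enrolment is complete and the data are being evaluated, so this should be reported as a change to the stated analysis. The cost is one extra model and two degrees of freedom, with no new data.

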### Rheumatoid Arthritis and Muscle Strength

Body composition, particularly the amount of lean mass in the arms and legs, is associated with disability in RA patients. A large number of RA patients suffer from an increased loss of muscle mass with a significant impact on these patients’ quality of life [10]. This condition is commonly known as rheumatoid cachexia and has been reported in two-thirds of all RA patients, including patients with stable RA [11,12]. In geriatric patients, cachexia is associated with higher-than-normal concentrations of tumor necrosis factor-α (TNF-α), interleukin (IL)-1, and IL-6; a reduction in these proinflammatory cytokines is associated with weight gain [12,13]. The loss of body cell mass in RA patients is associated with proinflammatory cytokine–induced altered energy metabolism and intake despite a theoretically adequate diet [14,15].

In an x-ray computed tomography–based study, RA patients had a significantly higher body mass index and fat area but lower muscle area, muscle density, and muscle strength than healthy individuals. Furthermore, a higher degree of joint destruction and disease activity were shown to be associated with higher muscle deficits and impaired muscle strength [16]. Stucki et al [17] found that in patients with RA quadriceps muscle strength explained 12% of the variance in the self-reported activities of daily life, and women with RA were reported to have 20% lower quadriceps strength than the controls [18]. Isotonic and isometric hand exercise in RA patients can decrease pain and disease activity and increase muscle strength and function as well as quality of life [19]. Hand grip strength was shown to discriminate between various disease states of RA and seems to return to near-normative level when the disease is in remission [20].

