### Sample Size

The sample size was calculated to determine the difference in work ability between patients with high versus low disease activity. We estimate the percentage of patients with good work ability to be 40% in patients with high disease activity and 80% in patients with low disease activity. Furthermore, we estimate that 70% of the included participants will have a low disease activity. With an alpha risk of .05 and a beta risk of .2 accepted in a 2-sided test, 71 patients need to be included (results were obtained with nQuery Advisor 7.0, Statcon). With a 30% rate of loss assumed (because of noncompliance during physical tests, lack of understanding, or refusal to participate), a total of 100 included patients will be required.

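### The secondary logistic regression of work ability names no adjustment for disease activity, which the protocol itself relates to both muscle strength and work ability

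*Protocol article*

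**What the plan says.** The Statistical Analysis section of the protocol article tests the primary hypothesis, which concerns work ability and muscle strength in high versus low disease activity, with a Pearson chi-square test. Other group comparisons use t, Mann-Whitney, chi-square or Fisher tests, and metric associations use Pearson or Spearman correlation. As described, none of these takes a covariate. The one regression is described in a single sentence: "Binary logistic regression will be used to evaluate the impact of frailty, functional ability, and muscle strength on work ability". The section does not say whether this is one joint model or several, and names no covariate.

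Elsewhere the article ties disease activity to both sides of that regression:
- **Strength.** The background section on muscle strength cites a study in which joint destruction and "disease activity were shown to be associated with higher muscle deficits and impaired muscle strength". The primary hypothesis also expects strength to differ by disease activity.
- **Work ability.** The Sample Size section assumes good work ability in "40% in patients with high disease activity and 80% in patients with low disease activity".

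Disease activity is measured in every patient by the CDAI (Data Collection and Procedures). Sex and age are also recorded: "The demographic characteristics include gender, age, marital status".

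**The concern.** A variable related to both the exposure and the outcome can create an association between them even when the exposure does nothing. By the article's own account, disease activity stands in that position for muscle strength and work ability. The regression as described does not separate the two.

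This matters because of the intended use. The Conclusions of the abstract and the Discussion section on implications call strength and functional ability modifiable, and say that evidence of association may motivate further research and encourage interventions on strength and lower extremity function. If weaker patients report poorer work ability only because their disease is more active, the result gives no support to strength training as such. The Strengths and Limitations section concedes that a cross-sectional design cannot show causality. It does not mention confounding, and the regression sentence speaks of impact.

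**Working it through.** **1. The plan's own figure.** Inputs from Sample Size: "With an alpha risk of .05 and a beta risk of .2 accepted in a 2-sided test, 71 patients need to be included"; 40% versus 80%; "we estimate that 70% of the included participants will have a low disease activity", so 30% high and an allocation ratio k = 7/3.

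Overall proportion with good work ability: 0.3 × 0.4 + 0.7 × 0.8 = 0.68.

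Patients in the high-activity group, without continuity correction:

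n = [1.96·√((1 + 1/k)·0.68·0.32) + 0.842·√(0.4·0.6 + 0.8·0.2/k)]² / 0.4² = 15.2, rounded up to 16.

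The low-activity group is then 38, giving 54 in total. With continuity correction it is 19 + 45 = 64. The stated 71 is not reproduced; it exceeds what 80% power needs and is close to the 70 obtained for 90% power without correction. For the loss, 71/0.7 = 101.4, near the stated total: "a total of 100 included patients will be required". The mismatch is a separate matter and does not bear on this point. From here 71 and 100 serve only as the range of analysable patients.

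**2. How far disease activity alone can produce a strength result.** Simulation, 2000 samples per setting:
- 30% high and 70% low activity, good work ability 40% and 80% (both from Sample Size);
- strength normal with unit SD within groups, lower by d SD in high activity, and with no effect of its own on work ability.

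The value of d is an assumption, shown as a range. The table gives the share of samples with P < .05 for strength and the median unadjusted odds ratio per within-group SD.

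| d (SD) | N=71, strength only | N=100, strength only | Disease activity added, N=71 / N=100 | Odds ratio, strength only |
|---|---|---|---|---|
| 0 | 4% | 4% | 4% / 5% | 1.0 |
| 0.3 | 7% | 7% | 4% / 4% | 1.1 |
| 0.5 | 10% | 14% | 5% / 5% | 1.2 |
| 0.8 | 18% | 26% | 5% / 4% | 1.3 |
| 1.0 | 24% | 35% | 4% / 5% | 1.4 |

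**3. If strength, function and frailty share one model.** Function and frailty can act as partial stand-ins for disease activity. Assume that they too have no effect of their own. At N=100:
- both 1 SD worse in high activity: the rate for strength falls from about 37% to 21% at d = 1.0, and from 14% to 10% at d = 0.5;
- both 0.5 SD worse: it falls from about 39% to 34% at d = 1.0.

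The starting values differ from the table by simulation error. A joint model reduces the excess but does not remove it.

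**4. Room for covariates.** The smaller outcome class (work ability not good) is 32%: 0.32 × 71 = 22.7 and 0.32 × 100 = 32 patients. Outcomes per parameter:
- one exposure plus CDAI: 22.7/2 = 11.4 to 32/2 = 16;
- one exposure plus CDAI, age and sex: 22.7/4 = 5.7 to 32/4 = 8;
- all three exposures plus CDAI, age and sex: 22.7/6 = 3.8 to 32/6 = 5.3.

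**The case against.** **The article is silent; it does not say the model is unadjusted.** This is largely right. A journal article may leave a covariate list to a fuller plan, so one cannot say that the model contains only the three named terms, or that strength is pooled over the sexes. What remains is that the article names its predictors, leaves out disease activity, and itself supplies the two links that make the omission matter.

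**The aim is association, and the study is declared hypothesis-generating.** This stands in part. In the simulation a marginal association does exist, so a significant unadjusted result is not a false statement about association. It is misleading only when read as a reason to act on strength, which is the use that the article foresees, in cautious words.

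**Adjusting for CDAI is not self-evidently right.** The background also reports that hand exercise can lower disease activity, so CDAI could lie partly downstream of strength. This is why the unadjusted result should be kept beside the adjusted one.

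**Stronger readings that the article does not support.**
- A reader might infer that sex or age confounds by the plan's own premises. No section links sex to work ability, and the 20% strength deficit in the background compares women with RA to controls, not to men. The frailty instrument's formula ("DFactor scores will be calculated with the gender-specific SHARE-FI formula") shows only that sex matters to that score. Age is linked to reduced strength, but not to work ability.
- A reader might infer that the primary chi-square test must be adjusted. Disease activity is the exposure there, so it cannot also be the covariate, and the article names no factor that is related to both disease activity and work ability.

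**Conclusion.** The point holds for the secondary regression. The article names no adjustment for disease activity although it relates disease activity to both strength and work ability, so a strength association could reflect disease activity alone.

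The size depends on an assumption that the article does not supply. With a strength deficit of 0.3 to 1.0 SD in high activity, the article's 40%/80% rates and 30/70 split, and no own effect of strength, a strength-only model is significant in about 7-35% of samples of 71 to 100 patients, against 4-5% with disease activity included. At the low end of the range the excess is small, and it may be lower throughout if function and frailty are in the same model. The calculation covers strength only; no such figure was derived for functional ability or frailty as exposures. It also treats disease activity as two groups. The point does not touch the validity of the primary test.

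**What to change.** Replace the regression sentence with a specification along these lines: muscle strength, functional ability and frailty are each fitted in their own binary logistic model of good work ability, with continuous CDAI as a prespecified covariate, and each adjusted odds ratio is reported with its confidence interval beside the unadjusted one. Separate models also avoid splitting strength over two terms, since grip strength is a component of the frailty score. Age and sex are added as the number of outcomes allows, under a rule fixed before the models are run. The conclusions on strength interventions should rest on the adjusted result.

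No new data are needed, because CDAI, age and sex are already collected. The cost is fewer outcomes per parameter: about 11-16 with one exposure plus CDAI, and about 6-8 with age and sex added, so the covariate list must stay short. The article reports that enrollment is complete and data are being evaluated. If the models have already been run, the adjusted analysis should be labelled as added after that point.
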